### Inclusion criteria

The women recruited will be those who have given written informed consent, who are in active labour with a singleton pregnancy, defined as regular uterine contractions of at least 2 in 10 minutes and cervical dilatation of at least 3 cms, with fetal gestational age of 37-42 weeks and a minimum weight of 60 kg. Competent women of sixteen years old or older are eligible. Both multiparous and nulliparous women will be eligible including those who have either gone into labour spontaneously or who have had an amniotomy and intravenous oxytocin to induce labour.

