## Measurements

• *General demographics*. Age, weight, gestational age, cervical dilatation at first request for analgesia, frequency of contractions, parity, spontaneous or induced labour, use of syntocinon, presentation, mode of delivery, drug administration to delivery interval. This information will be derived from the maternal notes and interview with the midwife taking care of the parturient.

• *Maternal Pain Evaluation*. Pain severity during last contraction will be assessed using a visual analogue score (VAS) (with anchor points of 0 = no pain at all and 10 = the most excruciating pain) and verbal scales of pain intensity during the last contraction (pain intensity score: 0 = no pain; 1 = mild pain; 2 = moderate pain; 3 = severe pain). In addition, the midwife will assess pain relief during the previous 30 minutes (pain relief score: 0 = none; 1 = slight; 2 = moderate; 3 = good, 4 = complete).

• *Maternal Sedation and Vomiting Evaluation*. Maternal sedation during the previous 30 minutes will be assessed by the midwife using sedation scores (0 = alert; 1 = mild i.e. occasionally drowsy and easily aroused; 2 = moderate sedation i.e. frequently drowsy but still easily aroused; 3 = severe sedation i.e. somnolent and difficult to rouse) and by measuring maternal oxygen saturation by pulse oximetry. Maternal pulse oximetry measurement is integral within the cardiotocograph (CTG) machine (Phillips PN/2703A) at the RUH and using the Masimo Rad 5 machine at PHFT. Vomiting will be assessed as a side effect with a yes/no answer pre-dose and during each subsequent thirty minutes period.

Maternal assessments will be made when the woman first requests analgesia and then every thirty minutes after the trial drug has been given, for a maximum of three hours or until delivery has occurred or additional analgesia is requested. A further 3 hours of measurements are then made if additional opioid analgesia is requested not less than 2 hours after the first dose. The parturient's overall satisfaction with the analgesia will also be assessed 12-24 hours post partum as well as their wish to choose the same opioid for their next labour analgesia.

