##### Other

(e) Maternal sedation score over first 3 hours

(f) Time from first dose to delivery

(g) Entonox or regional analgesia given

(h) Nausea over 3 hours

(i) Vomiting over 3 hours

(j) Oxygen saturation over 3 hours after each dose of study drug or until delivery

(j) Percent reporting that they would choose the same pain relief in their next pregnancy

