## Statistical Analysis

Women will be analysed in the group to which they were originally randomised, regardless of what subsequently occurred during their labour. To enable this, where appropriate, all measures will be collected on all women once they have been randomised. However, within this framework, women could still, at any time, withdraw their consent to be in the trial.

Data will be analysed using SPSS for Windows and MLWin [14]. Significance tests will use a 5% two-sided significance level. Randomisation will be stratified by study site, and this will be controlled for in all analyses. Given the design of the trial, it is anticipated that missing data will be mostly negligible. The exception will be for the observations taken at 30 minute intervals after administration of the trial drug, where observations will cease if the mother delivers. We will assume these missing data are "missing at random" [15]. Analysis of the two maternal primary outcome measures will be as follows. Pain relief will be measured at 30 minute intervals over 3 hours. The repeated measures nature of the data will be taken into account using a maximum likelihood based multi-level (mixed) model [14]. This model permits analysis of unbalanced repeated measures data thus avoiding exclusion of participants with incomplete data [14]. Initially the interaction between trial group and timing of pain VAS measurement will be tested to see if the effects of the study drug change over time. If the interaction effect is not statistically significant, the interaction will be removed from the multi-level model and the main effect of trial group tested. Parameter estimates with 95% confidence intervals will be presented. The second maternal primary outcome measure, mean difference in pain relief at 60 minutes, will be estimated using multiple regression.

The neonatal primary outcomes, need for resuscitation and Apgar score under 7 at 1 minute, will be compared between groups using logistic regression, and the results presented as odds ratios (95% CI) and Numbers Needed to Treat (NNT).

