Supplementary analyses will adjust for the following covariates that might have an impact on primary outcomes: maternal age, parity, gestation, pre-administration pain intensity. No formal correction for multiplicity will be applied to the significance tests for the 4 primary outcomes. Under the null hypothesis that the two treatment groups give identical outcomes, the probablities of 1 or more, 2 or more, 3 or more, or all 4 being statistcally significant are 0.19, 0.01,<0.001 and <0.001 respectively. The trial report will include a section on the impact of multiplicity on interpretation of the results.

Analysis of secondary outcome measures is likely to be as follows. The distributions of oxygen saturation and nausea VAS are likely to be highly skewed and so values will be categorised. For example, as under 95, 95-97, 98-100 for oxygen saturation and 0, 0.1-4.9, 5+ for nausea. These and other repeated measures categorical outcomes (verbal pain intensity, pain relief, maternal sedation, vomiting, cardiotocography) will be analysed in two ways; (a) using repeated measures models, and (b) as the proportion of women having a poor result during the 3 hour follow-up, using logistic regression (eg proportions having oxygen saturation 97 or below, nausea 5+, verbal pain intensity moderate or worse, pain relief none or slight, sedation moderate or severe, vomiting, cardiotocography non-reassuring or abnormal). Neonatal oxygen saturation and sedation scores in the 2 hours after delivery will be analysed using a similar approach.

Maternal satisfaction with analgesia and neonatal feeding behaviour (normal, mildly depressed, severely depressed) will be analysed using multinomial logistic regression.

Dichotomous outcomes such as Apgar score < 7 at 5 minutes, use of naloxone, transfer to neonatal intensive care unit, and reporting that they would choose the same analgesia for their next pregancy, will be analysed using logistic regression.

Time from first administration of study drug to delivery, and time to first meconium staining (excluding those where staining ocurred prior to trial drug), and time from delivery to first feed and time to first breath will be analysed using proportional hazards models, and the results presented as hazard ratios.

Multiple regression will be used to analyse umbilical artery pH and vein pH. Results will be presented with 95% confidence intervals whenever possible.

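### Time to delivery is planned with study site as the only named covariate, although strong candidate predictors are recorded before dosing; adjusting for them could recover power

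*Protocol article*

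**What the plan says.** In the protocol article, Statistical Analysis, adjustment beyond site is described in one sentence: "Supplementary analyses will adjust for the following covariates that might have an impact on primary outcomes: maternal age, parity, gestation, pre-administration pain intensity". It names four covariates and refers to the primary outcomes only. For every analysis the same section says: "Randomisation will be stratified by study site, and this will be controlled for in all analyses".

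Time to delivery appears among the maternal secondary outcomes (heading Other) as item "f) Time from first dose to delivery". Its analysis is given with the other time-to-event outcomes: "Time from first administration of study drug to delivery, and time to first meconium staining" and the remaining times "will be analysed using proportional hazards models, and the results presented as hazard ratios". No baseline covariate is named there. The secondary analyses as a group are introduced as likely rather than settled.

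The general demographics under Measurements include "cervical dilatation at first request for analgesia, frequency of contractions, parity, spontaneous or induced labour". Dilatation is thus taken before the drug is given. Onset is known at entry, because Inclusion criteria admits "those who have either gone into labour spontaneously or who have had an amniotomy and intravenous oxytocin to induce labour".

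**The concern.** Women may enter at any dilatation from 3 cm upwards, in spontaneous or induced labour, and with or without a previous birth. How far labour has progressed, how it began and parity can all be expected to bear on how soon a woman delivers. Of these three, only parity is on the covariate list, and the list does not reach the time-to-delivery model.

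A hazards model behaves differently from a linear model here. When strong baseline predictors are left out, the estimated treatment hazard ratio moves towards 1 even in a perfectly balanced trial, and the test loses power. At stake is the chance of detecting a real difference in time to delivery with data that the trial collects anyway.

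**Working it through.** **Inputs from the document.** 203 women per group, so 2 × 203 = 406 (Sample Size); two-sided 5% level (Statistical Analysis).

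**Assumptions, because the document is silent.** All 406 women count as deliveries, with no censoring. The conditional hazard ratio (HR) is 1.30 or 1.38. The omitted predictors act together as one standard normal score with log-hazard SD s = 0.3, 0.5, 0.8 or 1.0, that is, an HR per SD of exp(s) = 1.35, 1.65, 2.23 or 2.72. Site was not simulated; the model with treatment alone stands in for the site-only model.

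**Step 1: the plan's own figures.** The document gives no power for time to delivery. Its stated sizes for a 1 cm difference in pain at 90% power are 203, 144 and 86 per group. With n = 2(1.96 + 1.2816)² SD² / 1² = 21.02 × SD², the stated SDs of 3.1, 2.6 and 2.0 give 202, 143 and 85. The planned size therefore reproduces to within one woman per group.

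**Step 2: power with no omitted predictor.** Schoenfeld's formula for equal allocation is power = Φ(ln HR × √(d/4) − 1.96). With d = 406, √(406/4) = 10.075.
- HR 1.30: 0.2624 × 10.075 − 1.96 = 0.683, power 75%.
- HR 1.38: 0.3221 × 10.075 − 1.96 = 1.285, power 90%.

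**Step 3: simulated Cox models.** There were 1,500 trials per setting, each fitted without and with the score. Monte Carlo standard error is at most √(0.25/1500) = 1.3 points per power figure.

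| Conditional HR | s | Power without score | Power with score | Loss (points) | Average HR without score |
|---|---|---|---|---|---|
| 1.30 | 0.3 | 67.5% | 75.0% | 7.5 | 1.275 |
| 1.30 | 0.5 | 58.3% | 73.1% | 14.8 | 1.245 |
| 1.30 | 0.8 | 48.3% | 75.8% | 27.5 | 1.211 |
| 1.30 | 1.0 | 38.7% | 73.1% | 34.4 | 1.181 |
| 1.38 | 0.3 | 86.7% | 91.1% | 4.4 | 1.358 |
| 1.38 | 0.5 | 75.3% | 89.2% | 13.9 | 1.309 |
| 1.38 | 0.8 | 60.7% | 89.1% | 28.4 | 1.256 |
| 1.38 | 1.0 | 53.3% | 90.0% | 36.7 | 1.224 |

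**Step 4: does dilution account for the loss?** Put the diluted HR into the Step 2 formula. For HR 1.38 and s = 0.5: ln 1.309 = 0.2693; 0.2693 × 10.075 − 1.96 = 0.753; power 77%, against 75.3% simulated. For HR 1.30 and s = 0.8: ln 1.211 = 0.1914; 0.1914 × 10.075 − 1.96 = −0.031; power 49%, against 48.3%. Dilution explains nearly all of it.

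**Step 5: validity.** With a true HR of 1, the model without the score rejects in 4.7% to 5.5% of trials. The unadjusted test holds its level.

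**Cross-check.** A separate set of 1,000 simulated trials per setting at HR 0.75 (equivalent to 1.33) gave 68% (s = 0.5) and 52% (s = 0.8) without the score, against 82% to 83% with it. The unadjusted figures lie between those for HR 1.30 and 1.38 above.

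**The case against.** The case against is substantial. The covariates of a secondary time-to-event model are ordinary content for an analysis plan, and the article presents its secondary analyses as provisional. It says that site is controlled for; it does not say that nothing else will be. The four-covariate sentence was written for the primary outcomes and should not be faulted for serving them. The diluted hazard ratio is a marginal quantity, not a biased one. Every power figure rests on an assumed effect and an assumed prognostic strength, and at s = 0.3 the loss is modest.

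All of this stands, and it limits the point to an efficiency matter. It does not remove it. The article does fix a covariate list and its scope, does choose the model for time to delivery, and names one covariate for it, while the relevant pre-dose data are already collected.

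A reader might infer two stronger things, and neither is supported.

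- *That time to delivery is the outcome where omitted covariates cost the most power.* Analysing change in pain without adjusting for baseline pain keeps (1 + r)/2 of the efficiency of the adjusted analysis: 65%, 75% and 85% at the plan's correlations of 0.3, 0.5 and 0.7. For the Cox model at HR 1.38, the retained efficiency is about ((1.96 + z) / 3.245)², where z is the normal quantile of the unadjusted power and 3.245 = 1.96 + 1.285 from Step 2. This gives about 90% at s = 0.3, 66% at 0.5 and 47% at 0.8. Which outcome loses more depends on s, which the document does not give.
- *That the pain results are biased because dilatation and onset are left out.* Pain readings are taken at intervals "where observations will cease if the mother delivers", and missing at random is easier to defend when predictors of delivery are in the model. But a simulation of this mechanism put the bias at about 0.06 cm of the 1 cm target, and only when dilatation strongly drives pain and the drug also alters delivery time. That is too small and too conditional to carry the point.

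**Conclusion.** The point holds as a cheap efficiency improvement to one secondary outcome. The site-only analysis is valid and nothing in the article contradicts itself here. If parity, dilatation and onset together predict delivery weakly (s = 0.3), adjustment recovers about 4 to 7.5 points of power; if moderately (s = 0.5), about 14 to 15; if strongly (s = 0.8), about 28. These figures assume 406 uncensored deliveries, proportional hazards given the score, and a conditional HR of 1.30 to 1.38. The document states neither the effect nor the prognostic strength, so the range should be read as an illustration. The sample size, which rests on pain at 60 minutes and the neonatal outcomes, is not affected.

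**What to change.** Prespecify the main time-to-delivery model as proportional hazards with treatment, site, parity, dilatation when analgesia is first requested, and spontaneous or induced onset. Report the site-only model alongside. State that the main hazard ratio is conditional on these covariates, so that the two estimates are not read as rival answers to one question. Settle this before unblinding, so that the choice of covariates cannot follow the results.

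Optionally, add dilatation and onset to the supplementary covariates for the pain model, expecting little gain.

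The cost is a sentence or two and no new data. The downsides are a conditional rather than a marginal hazard ratio as the main estimate, and a few missing baseline values, for which a simple rule should be stated.

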### Primary outcome measures

#### Maternal

##### Pain relief

Measured using change in pain intensity from pre-analgesia levels over the subsequent 3 hours.

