##### Pain relief at 60 minutes

Measured by change from baseline in pain intensity VAS at 60 minutes. The dose of analgesia is administered intra-muscularly, and it is anticipated that maximum analgesic effect will occur at around 60 minutes after administration. Pain intensity at 60 minutes was the primary outcome used by Fairlie et al [10], and is the basis of our sample size calculation.

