#### Neonatal

##### Side effects

(a) Need for neonatal resuscitation

(b) Apgar Score <7 at 1 minute

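### The quoted null probabilities for the four primary outcomes assume independent tests without saying so; the outcome definitions contradict this, so the figures for two or more and three or more are too low

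*Protocol article*

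**What the plan says.** All references are to the protocol article.

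- Statistical Analysis sets the test level: "Significance tests will use a 5% two-sided significance level".
- The same section declines adjustment: "No formal correction for multiplicity will be applied to the significance tests for the 4 primary outcomes". It then states that, under the null hypothesis, "the probablities of 1 or more, 2 or more, 3 or more, or all 4 being statistcally significant are 0.19, 0.01,<0.001 and <0.001 respectively", and promises that the trial report will discuss how multiplicity affects interpretation. Independence of the tests is not mentioned.
- Primary outcome measures, maternal: the first outcome is "Measured using change in pain intensity from pre-analgesia levels over the subsequent 3 hours" and the second is "Measured by change from baseline in pain intensity VAS at 60 minutes". On the schedule, Statistical Analysis says "Pain relief will be measured at 30 minute intervals over 3 hours".
- Primary outcome measures, neonatal: "a) Need for neonatal resuscitation" and "Apgar Score <7 at 1 minute".

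The only correlations in the document are the 0.3, 0.5 and 0.7 under Sample Size. They relate pain scores before and after analgesia, not one primary outcome to another.

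**The concern.** The null hypothesis of identical outcomes in the two groups does not make four tests independent. Readings every 30 minutes over 3 hours give six post-dose readings, and the 60-minute reading is one of them. Both maternal outcomes also subtract the same baseline in the same women. That overlap is built into the definitions and needs no outside evidence. The two neonatal outcomes are measured on the same babies around birth, so positive correlation is to be expected there too, though the document does not say how strong it is.

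Positive correlation makes false positives cluster. It lowers the chance of at least one, and raises the chance of two or more and of three or more. The most natural multiple success in this trial is both pain outcomes together, or both neonatal outcomes together, and that is the pattern for which the stated figure is too small. These probabilities are the plan's only quantitative statement on multiplicity, and the promised section of the report could easily take them over.

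**Working it through.** **Inputs from the document.** Four primary tests, each two-sided at 5%, uncorrected (Statistical Analysis). Two maternal and two neonatal outcomes, defined as above.

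**Inputs that are assumed.** The correlation ρ between the two test statistics within each pair, and independence between the maternal and the neonatal pair.

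**Step 1: reproduce the stated figures.** With X the number of significant tests and X ~ Binomial(4, 0.05):

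- P(X ≥ 1) = 1 − 0.95⁴ = 0.1855
- P(X ≥ 2) = 0.1855 − 4 × 0.05 × 0.95³ = 0.1855 − 0.1715 = 0.0140
- P(X ≥ 3) = 4 × 0.05³ × 0.95 + 0.05⁴ = 0.00048
- P(X = 4) = 0.05⁴ = 0.000006

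Rounded, these are the plan's 0.19, 0.01, <0.001 and <0.001.

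**Step 2: allow correlation within pairs.** Let q = P(|Z₁| > 1.96 and |Z₂| > 1.96) for a bivariate normal pair with correlation ρ. Within a pair, the probabilities of 0, 1 and 2 significant results are 0.90 + q, 0.10 − 2q and q. The two pairs are then combined.

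Example, ρ = 0.8 in both pairs: q = 0.02194, so the pair probabilities are 0.92194, 0.05612 and 0.02194.

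- P(X ≥ 1) = 1 − 0.92194² = 0.1500
- P(X ≥ 2) = 0.1500 − 2 × 0.92194 × 0.05612 = 0.1500 − 0.1035 = 0.0466 (unrounded terms)
- P(X ≥ 3) = 2 × 0.05612 × 0.02194 + 0.02194² = 0.0029
- P(X = 4) = 0.02194² = 0.0005

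| ρ in both pairs (assumed) | 1 or more | 2 or more | 3 or more | all 4 |
|---|---|---|---|---|
| 0 (the plan) | 0.185 | 0.014 | 0.0005 | 0.00001 |
| 0.3 | 0.181 | 0.018 | 0.0009 | 0.00002 |
| 0.5 | 0.173 | 0.025 | 0.0016 | 0.0001 |
| 0.7 | 0.160 | 0.037 | 0.0025 | 0.0003 |
| 0.8 | 0.150 | 0.047 | 0.0029 | 0.0005 |
| 0.9 | 0.136 | 0.060 | 0.0033 | 0.0009 |

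**Step 3: use only the overlap that the definitions guarantee.** Leave the neonatal pair fully independent. If the six post-dose readings have equal variances and a common within-woman correlation w (assumed), the 60-minute reading correlates with their mean by √[(1 + 5w)/6]. This is 0.65 for w = 0.3, 0.76 for w = 0.5 and 0.87 for w = 0.7. With ρ between 0.65 and 0.87 in the maternal pair alone, P(X ≥ 2) is 0.024 to 0.034 and P(X ≥ 3) is 0.0016 to 0.0027.

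**Step 4: correlation between the pairs.** In simulation (2,000,000 draws), a between-pair correlation of 0.1 or 0.2 leaves P(X ≥ 2) almost unchanged: 0.037 to 0.038 at ρ = 0.7 and 0.046 to 0.047 at ρ = 0.8. It raises the rarer tails somewhat. With 0.2 between pairs and ρ = 0.9 within, P(X ≥ 3) is 0.0047 and P(X = 4) is 0.0014.

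**The case against.** The best defence is that nothing operational depends on these figures. No significance level, decision rule, sample size, estimate or interval uses them. The plan openly declines correction, discloses a 0.19 chance of at least one false positive, and commits the report to discussing multiplicity. Under positive correlation 0.19 is on the safe side. All of this stands, and it limits the importance of the point.

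A reader might go further than the document allows in four ways.

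- **Taking 0.04 to 0.05 as the true probability of two or more.** That needs ρ of about 0.73 to 0.83 in both pairs. A high maternal value is plausible, but the neonatal value is unknown. With 0.8 in the maternal pair, a neonatal 0.3 gives 0.032 and 0.5 gives 0.036.
- **Calling it a three- to five-fold understatement.** Against the unrounded 0.0140, ρ of 0.5 to 0.9 gives ratios from 0.025/0.014 = 1.8 to 0.060/0.014 = 4.3. A factor near 5 comes from dividing by the rounded 0.01.
- **Quoting an upper limit of 0.10.** That limit (0.0975) needs perfect dependence in both pairs. If event rates of 30% and 25%, as under Sample Size, apply to the same babies, the correlation between the two neonatal outcomes cannot exceed √[(0.25 × 0.70)/(0.75 × 0.30)] = 0.88.
- **Predicting that a paired result will be reported as a 1-in-100 event.** The plan does not say this.

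It is also fair that the six-reading mean simplifies the planned test. The plan tests the group-by-time interaction first and the main effect only if that is not significant, and later readings stop at delivery. This weakens any single value of ρ. It does not restore independence between the 60-minute outcome and a series that contains it.

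**Conclusion.** Wrong as written, with moderate consequence. The four figures reproduce as independence figures, the assumption is unstated, and the plan's own maternal definitions rule it out. Two of the four are too low over the range considered: for ρ of 0.5 to 0.9 in both pairs, two or more is about 0.025 to 0.06 rather than 0.01, and three or more about 0.0016 to 0.0033 rather than below 0.001. Both also fail with only the maternal pair correlated.

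The other two do not mislead in the same way. One or more falls to about 0.14 to 0.17, and all four stays below 0.001 up to ρ = 0.9 provided the pairs are independent of each other. At weak correlation the error is small: with ρ = 0.3 in both pairs, two or more is 0.018 and three or more is still 0.0009.

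That correlation exists in the maternal pair follows from the document. Its size, and any correlation in the neonatal pair, are assumptions. Correction is worthwhile, but the trial's design and its analyses do not hang on it.

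**What to change.** 1. Either state that the four probabilities hold only for independent tests and add a range over plausible correlations, labelled as assumed (one or more: about 0.14 to 0.19; two or more: roughly 0.02 to 0.06; three or more: up to about 0.003 with the pairs independent of each other), or delete the figures.
2. Add that two significant results within the maternal pair, or within the neonatal pair, are not independent confirmation of an effect.
3. Optionally, obtain the probabilities at analysis by re-randomising allocation within site jointly across the four observed outcomes. This keeps their actual correlation and can follow the planned two-stage test of the 3-hour outcome.

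The cost is a sentence or two, plus one re-randomisation run if item 3 is adopted. Outcomes, sample size and planned tests are unchanged. The stated figures for two or more and three or more become less favourable.

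### Verbal pain, sedation, vomiting and maternal oxygen saturation are recorded before dosing, but the secondary analyses do not say that the pre-dose value is used, which costs precision without biasing the comparison

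*Protocol article*

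**What the plan says.** All from the protocol article.

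- **Measurements, timing:** "Maternal assessments will be made when the woman first requests analgesia and then every thirty minutes after the trial drug has been given". This covers the verbal pain scale and the sedation score.
- **Measurements, sedation and vomiting:** the sedation evaluation is also done "by measuring maternal oxygen saturation by pulse oximetry", so saturation falls under the same pre-dose assessment. For vomiting the pre-dose reading is explicit: "Vomiting will be assessed as a side effect with a yes/no answer pre-dose and during each subsequent thirty minutes period".
- **Statistical Analysis, secondary outcomes:** the paragraph opens "Analysis of secondary outcome measures is likely to be as follows". It names two routes for the repeated categorical outcomes. Route (a) is repeated measures models, with no further detail. Route (b) treats each outcome "as the proportion of women having a poor result during the 3 hour follow-up, using logistic regression". Example cut-points for route (b) are saturation of 97 or below, at least moderate verbal pain, moderate or severe sedation, and any vomiting.
- **Statistical Analysis, covariates:** study site is the one factor named for every analysis. Beyond that, "Supplementary analyses will adjust for the following covariates that might have an impact on primary outcomes: maternal age, parity, gestation, pre-administration pain intensity".
- **Pre-existing states elsewhere:** the primary pain outcomes are changes from the pre-analgesia level, and the meconium analysis leaves out women whose staining came before the trial drug.

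**The concern.** The pre-dose state is collected for all four measures, but no use of it is stated for route (b), and route (a) is silent on whether it is a response, a covariate or unused. A woman who was vomiting or at a saturation of 97 or below before the injection, and who is so again afterwards, counts as a poor result just like a woman in whom it began after the drug.

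These outcomes carry the maternal side-effect comparison and a further measure of pain. Mixing persistent with new-onset cases pulls the odds ratio towards 1, raises the absolute rates in both arms and makes a real difference easier to miss. At least moderate verbal pain at any time in 3 hours is probably the most exposed, because women enter when they ask for an opioid in active labour. That is an inference; no rate is given.

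The same paragraphs deal with a pre-existing state for meconium but not for vomiting, which is recorded before dosing for exactly this kind of comparison.

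**Working it through.** **1. The plan's own figures.** None depends on the secondary analyses. The only pre/post correlations in the document are those used for the VAS in the Sample Size section, and they reproduce. SD of change = 2.6 × √(2(1 − ρ)) gives 3.08, 2.60 and 2.01 for ρ = 0.3, 0.5 and 0.7 (stated 3.1, 2.6, 2.0). With the stated SDs, a 1 cm difference, 90% power and two-sided 5%, the t-based n per group is 202.9, 143.03 and 85.03, rounded up to 203, 144 and 86 as stated.

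**2. Continuous analogue.** Assume those correlations carry over to a secondary measure. Adjusting for baseline multiplies the variance of a post-dose comparison by 1 − ρ²: 0.91, 0.75 and 0.51. With SD 2.6 and 203 per group, the unadjusted SE is 2.6 × √(2/203) = 0.258. Adjusted, it is 0.246, 0.223 and 0.184. Equivalently, 203 × (1 − ρ²) = 184.7, 152.3 and 103.5 women per group would match 203 unadjusted.

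**3. Route (b), limiting case.** Assume new-onset rates of 30% v 16% (the neonatal resuscitation rates, borrowed only as an example effect) and that every woman poor before dosing is poor again afterwards. With share s poor before dosing, the observed rate is s + (1 − s)p. For s = 0.2: 0.2 + 0.8 × 0.30 = 0.440 and 0.2 + 0.8 × 0.16 = 0.328, so the odds ratio is (0.328/0.672)/(0.440/0.560) = 0.62.

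| s | Observed rates | Odds ratio | Power, all women, unadjusted | Power, women not poor before dosing |
|---|---|---|---|---|
| 0 | 30.0% v 16.0% | 0.44 | 0.92 | 0.92 |
| 0.1 | 37.0% v 24.4% | 0.55 | 0.79 | 0.89 |
| 0.2 | 44.0% v 32.8% | 0.62 | 0.64 | 0.85 |
| 0.3 | 51.0% v 41.2% | 0.67 | 0.51 | 0.80 |

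**4. Route (b), 80% persistence.** Simulated logistic regression, 203 per group, 1500 runs, same new-onset rates, with the drug making no difference in women already poor. For s = 0.1, 0.2 and 0.3, power without and with the baseline state is 0.82 v 0.88, 0.66 v 0.79 and 0.52 v 0.66, gains of about 6, 13 and 14 points. With no drug difference, the rejection rate is 0.041, 0.041 and 0.047 unadjusted and 0.047, 0.046 and 0.040 adjusted, so the type I error is not inflated either way.

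**5. Route (b), less favourable assumptions.** Assume overall rates of 40% v 27%, with a yes/no baseline linked to the outcome by a latent correlation of 0.3, 0.5 or 0.7. With 20% poor before dosing, power goes from 79.8% to 81.6%, 78.8% to 83.4% and 79.2% to 88.5%. With only 2% or 5% poor before dosing, it rises by about 0.3 to 2 points (for example 80.1% to 80.4%, and 80.4% to 82.5%).

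**The case against.** The strongest reply is that this is a journal article, that the secondary analyses are openly provisional, and that covariate terms in secondary models are commonly left to the statistical analysis plan. Nothing is contradicted or miscalculated. This stands in part. It rules out saying that the plan never uses the pre-dose values: route (a) is silent, and naming site for every analysis does not say that nothing else enters. It does not dispose of route (b), where the article gives the endpoint, example cut-points and model, and ties its covariate list to the primary outcomes. Using a baseline that is already collected improves on that stated method.

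A reader might also infer that pre-existing symptoms count against one drug. The documents do not support that. Allocation is randomised and blinded, both arms receive an opioid, and such symptoms fall equally on both in expectation. Nor does a pre-dose symptom count by itself: route (b) looks at the follow-up window, so it counts only if present again after dosing.

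Three further points stand. The sizes rest on assumed rates and on correlations borrowed from VAS pain. Where the pre-dose state is rare, as moderate or severe sedation may be given that recent parenteral opioid use is an exclusion, the gain is negligible. And a covariate alone leaves the outcome definition unchanged, so it does not separate drug-related from pre-existing symptoms.

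**Conclusion.** The point holds as a matter of precision and interpretation in secondary outcomes. Route (b) states no use of pre-dose values that the trial collects, and route (a) leaves their role open. The comparison between arms stays valid, and no sample size or power figure in the article changes. The loss is a diluted contrast, higher absolute rates in both arms and lower power. Its size cannot be derived from the documents: under the assumptions shown, adjustment in route (b) gains from under 1 percentage point (rare pre-dose state, weak correlation) to about 14 (30% already poor, 80% persistence, no drug effect in those women). The upper figures rest on the most favourable assumptions and should not be read as expected gains.

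**What to change.** In the secondary-outcome paragraphs of Statistical Analysis, state that the pre-dose value of the same measure (verbal pain score, sedation score, vomiting yes/no, oxygen saturation) is included as a covariate with site in both routes (a) and (b). Add a simple rule that keeps women whose pre-dose value is missing, such as a missing indicator or the mean value.

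To separate drug-related from pre-existing symptoms, also report new-onset or worsened events among women not in the poor category before dosing, following the approach already taken for meconium staining. For verbal pain this group may be small, so there the covariate matters more.

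The cost is a few sentences settled before unblinding, with no new data or participants. There are two small downsides. The adjusted odds ratio is conditional rather than marginal and should be labelled so. Where the pre-dose state is rare, the covariate adds little and may be too sparse to fit, so the plan should say beforehand what is done then.
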